**Table 2 Tab2:** Suubi+Adherence-R2 Study Measures

Variable	Measurement	Reliability	Timepoint
Demographics (Respondent: Adolescent Participant)			
Age; sex (assigned at birth), orphan status (single vs. double); socioeconomic status; family composition/structure; caregiver educational level	Socio-demographic questionnaire	n/a	^a^T1-RC, 12, 24, 36, 48
Moderators (Respondent: Adolescent Participant)			
Rural/urban/semi-urban; exposure to outside HIV/STI-related programs; economic/household income; asset accumulation			^a^T1-RC, 12, 24, 36, 48
Potential Mechanisms of Change (Respondent: Adolescent Participant)			
Self-efficacy	Adapted Tennessee Self-Concept Scale [147] (TSC-2) (*pretested in Suubi Studies*)	0.81	^a^T1-RC, 12, 24, 36, 48
Education plans/aspirations	Adapted Monitoring the Future Survey [148]	n/a	^a^T1-RC, 12, 24, 36, 48
Motivation to participate	Questions tested in previous studies [103, 124, 149, 150]	n/a	^a^T1-RC, 12, 24, 36, 48
Family Support	Social Support Behaviors Scale (SS-B) [151]Family Cohesion Scale [152], Krauss Interview [153]Parent Child Relationship Inventory (PCRI) [154]	0.77 0.69 0.91	^a^T1-RC, 12, 24, 36, 48
Family Stability	Socio-demographic questionnaire	n/a	^a^T1-RC, 12, 24, 36, 48
Hopelessness	Beck Hopelessness Scale [152]	0.79	^a^T1-RC, 12, 24, 36, 48
Self-esteem	Rosenberg Self-Esteem Scale [155]	0.77-0.88	^a^T1-RC, 12, 24, 36, 48
Condom Negotiation Self-Efficacy	Condom negotiation self-efficacy scale [156]	0.80	^a^T1-RC, 12, 24, 36, 48
Sexual Communication Skills	Sexual Communication Scale [157]	0.80	^a^T1-RC, 12, 24, 36, 48
Transitions (education, employment, residential independence, prosocial transition, relationship/marital status, pregnancy/parenthood	Demographics, MTF, Work history interview, Relationship assessment scale, Adolescent Sexual Behavior Assessment (ASBA), additional prosocial activities		^a^T1-RC, 12, 24, 36, 48
Social Support	Multidimensional scale of perceived social support MSPSS [158]	0.84	^a^T1-RC, 12, 24, 36, 48
Access to services	RBA Services [159], Treatment Services Review (TSR) teen and adult versions [160–162]	.66-.83	^a^T1-RC, 12, 24, 36, 48
Cost of staff time, supplies, overhead for IDAs	Project records; Admin. Review	n/a	ongoing
Substance misuse	Questions adapted from PhenX Toolkit [163], Alcohol, Smoking, and Substance Involvement Screening Test [164], DISC-IV modules, CIDI modules	n/a; 0.58-0.90	^a^T1-RC, 12, 24, 36, 48

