HIV stigma/disclosure	CASAH Social Disclosure Interview [165], Social impact scale [166]		^a^T1-RC, 12, 24, 36, 48
Cognitive function	Peabody Picture Vocabulary Test (PPVT) [167], Symbol Digit Modalities Test (SDMT) [168], Color Trails Test [169], WHO_UCLA Auditory Verbal Learning Test [170], Grooved Pegboard Test [171]	0.61-0.88, 0.76, 0.64-0.79, 0.66, 0.85-0.91	^a^T1-RC, 12, 24, 36, 48

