#### Time points used in inferential analyses

To maximize rigor, to assure alignment of cognitive functioning data (only measured in the *Suubi+Adherence-R2 study*) and our remaining outcomes, and to avoid reuse of *Suubi+Adherence* outcomes (already examined for shorter-term intervention efficacy) that would bias tests of longer-term intervention efficacy, all primary inferential analyses and most of the secondary inferential analyses listed will use only Suubi+*Adherence-R2* data. The exception is longitudinal developmental trajectory analyses to explore associations between changes in time-varying covariates and mechanisms of change with outcomes measured across both *Suubi+Adherence* and *Suubi+Adherence-R2*.

#### Primary Analyses for Aim 1

We hypothesize that participants in the *Suubi+Adherence* intervention group will exhibit a higher odds of HIV viral suppression relative to participants in the bolstered standard of care (BSOC) control condition (H1a) during Suubi+*Adherence-R2*. To test H1a, we will fit a three-level generalized linear mixed model (GLMM) with fixed effects for study arm, time, and their interaction. We will use random intercepts for Clinic ID to account for clustering of persons within clinics and include random intercepts, random slopes, and their covariance for person ID to account for clustering of repeated measurements within persons. Reflecting the binary HIV viral suppression outcome, a binomial distribution and logit link will be used. To test H1a we will perform a time-averaged comparison of repeatedly measured observations across study arms to examine intervention effects over the duration of the study period. Alpha will be set at .05 for this planned comparison.

#### Secondary Exploratory Analyses for Aim 1

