We anticipate that in the long run and during the social transition period for participants, YLHIV in the intervention group will report superior mean levels of protective health behaviors, improved financial outcomes related to successful uptake of the microfinance-based principles FEE, and lower negative health risk behaviors, as implied by Specific Aim 2. Relative to participants in the BSOC control condition, intervention group participants should, over time/during the transition period: H2(a) exhibit lowered mean levels of sexual risk behavior; H2(b) report increased mean levels of adherence self-efficacy; H2(c) increased mean economic stability; H2(d) increased mean levels of cognitive functioning, and H2(e) increased mean levels of mental health functioning, H2(f) increased mean levels of social support and H2(g) prosocial transition functioning. To test H2(a)-H2(g) we will fit linear mixed models (LMMs) using the same fixed effects (study arm, time, and study arm-by-time) and random effects for the clinic (random intercepts) and person levels (random intercepts, random slopes, and their covariance) as in the proposed H1 analyses described. To maintain a nominal Type 1 error rate of 5% across tests of H2(a)-H2(g), α will be set at .05/7=.007 for each planned time-averaged comparison. To maximize rigor, the assumptions of normality and constant variance of residuals for these continuous outcomes in LMMs will be evaluated by examining histograms of the residuals and scatter plots of predicted values-by-Cholesky-scaled residuals, respectively. Transformations of outcomes will be utilized as needed to improve data conformance with model assumptions. Inferences for models whose residual statistics still do not fully meet assumptions following transformations will be generated via robust heteroskedastic-consistent estimators [192]. All analyses will include outlier and influential case screening via computation of Cook’s D, DFBetas, and likelihood displacement statistics. If outliers are found, results will be reported with and without outliers included [193, 194].

#### Secondary exploratory analyses for Aim 2

The same GLMM approach described above for Aim 1’s primary analysis will be used to test whether the odds of STI acquisition during young adulthood is lower across time for intervention participants than control participants.

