##### Sex as a biological variable

In line with recent NIH guidelines on exploring sex differences in effects, all previously described inferential analyses will be repeated with models extended to include sex assigned at birth as a moderator to examine whether effects vary by participant sex.

#### Statistical Power Analysis for Aims 1 and 2

We used NCSS PASS [199] to compute minimum detectable effect size estimates for the primary hypotheses H1(a) and H2(a)-H2(g) proposed to fulfil Specific Aims 1 and 2, respectively. For all power analyses we assume power=.80 and 5 repeated assessments from N=450 participants conservatively assuming 20% attrition. For H1(a), based on our current *Suubi+Adherence* project’s data we further assumed a control proportion of 65% virally suppressed, α=.05, and an intraclass correlation (ICC) of .032 at the clinic level and .819 at the person level. Under these assumptions, the minimum detectable raw proportion difference is 13%, which corresponds to an odds ratio (OR) of 1.91 and a standardized effect estimate *h*=.29, which is between a small (*h*=.20) and medium (*h*=.50) effect size [200] The minimum detectable OR of 1.91 is less than ORs obtained in the *Suubi+Adherence* study [6] ensuring that we will have sufficient power to detect similar or slightly smaller effects in the project period. For H2(a)-H2(g), we computed the minimum detectable standardized mean difference *d* using the same inputs as listed above, α=.007, and a range of ICCs from .003 to .542 for change mechanisms based on data from the *Suubi+Adherence* study. Under these conditions *d* ranged from .10 to .13, which are small standardized effect sizes [201]. Taken collectively, our study will have sufficient power to detect small to small-medium effects across a wide variety of conditions.

#### Qualitative data analysis for Aim 3

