The study innovates in several ways. The study extends the evaluation of a “home-grown” intervention from a focus on short-term impacts to longer-term outcomes as adolescents transition through young adulthood—hence ascertaining the extent to which the short-term effects from FEE are sustained in the long run. To our knowledge, *Suubi+Adherence-R2* would be the first of its kind to measure the long-term efficacy of a FEE intervention for YLHIV. As such, the study will enable us to learn the extent to which participation in a FEE intervention may potentially change the would-be poor trajectory for YLHIV in low-resource communities. Suubi+Adherence-R2 will be one of few studies of YLHIV in SSA to use multiple measures of adherence. Adherence remains a primary barrier to actualizing the full potential of ART, and no assessment method has proven to be the “gold standard” or economically feasible for wide use, particularly in low resource settings. Suubi+Adherence will use virologic suppression as the primary outcome; and for secondary outcomes augment self-reports which are subject to memory and social desirability bias with use of unannounced pill counts. This will allow us to compare data from multiple measures to more accurately assess true adherence, extending work from adult HIV studies [50, 51]. Finally, Suubi+Adherence-R2 will identify significant pathways to both successful and problematic transitions and will determine strategic intervention points for YLHIV in SSA, one of the world’s poorest regions with the highest HIV prevalence rates. These results may be relevant for others from impoverished backgrounds coping with chronic health conditions for which the literature on this developmental transition is limited. New to this study will be the inclusion of cognitive functioning measures, which have previously been shown to impact ART adherence in other settings and which may be influenced positively by previous FEE intervention exposure.

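### The Aim 2 power statement covers cognition (H2(d)) with ICCs taken from the original study, which did not measure cognition; its ICC is an unlabelled assumption and H2(d) needs its own detectable effect

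*Protocol article*

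**What the plan says.** The section on statistical power for Aims 1 and 2 says software was used "to compute minimum detectable effect size estimates for the primary hypotheses H1(a) and H2(a)-H2(g"), so H2(d) is included. The primary analyses for Aim 2 define that hypothesis as "H2(d) increased mean levels of cognitive functioning". The inputs are power .80, 450 participants with 5 repeated assessments, and alpha .007 per Aim 2 test. The ICCs are described as "a range of ICCs from .003 to .542 for change mechanisms based on data from the" original study. The result is d from .10 to .13 for the whole set.

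On cognition, the section on time points restricts the main analyses to Round 2 data partly "to assure alignment of cognitive functioning data (only measured in the" Round 2 study). The Discussion agrees: "New to this study will be the inclusion of cognitive functioning measures".

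Table 2 lists five cognitive tests among the potential mechanisms of change, with reliabilities "0.61-0.88, 0.76, 0.64-0.79, 0.66, 0.85-0.91". It does not say what kind of reliability these are or over what interval.

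**The concern.** The power statement gives H2(d) a source for its ICC that the rest of the article rules out. This is more than detail left to a fuller document: it is a positive claim of power for a named hypothesis, with a stated origin that cannot be right.

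The within-person ICC matters because H2(d) is tested by a time-averaged comparison. The more alike a person's five yearly scores are, the less the repeats add and the larger the detectable difference. If cognition is more stable within a person than the mechanisms measured before, the joint range understates what H2(d) can detect.

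The stake is interpretation. Cognition is part of Aim 2 and is presented as an innovation of Round 2. If H2(d) is null, a reader relying on the power section would take a small effect to have been excluded. No sample-size decision depends on the figure, since the cohort is limited to the 702 original participants.

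**Working it through.** **Inputs.** From the power section: N = 450 in total (702 × .8 × .8 ≈ 449), m = 5 assessments, power .80, alpha .007, Aim 2 ICCs .003 to .542; for H1(a), clinic ICC .032 and person ICC .819. From the account of the original study: 39 clinics, so M = 450/39 ≈ 11.54 participants per clinic. From Table 2: cognitive reliabilities .61 to .91. Assumed: a two-sided test (sidedness is not stated), equal arms, and the .003 to .542 range read as person-level (the level is not stated).

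**Formula.** For a time-averaged comparison of two arms,

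d = (z₁₋α/₂ + z_power) × √{(4/N) × [(1 + (m − 1)ρ_person)/m + (M − 1)ρ_clinic]},

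with z₁₋α/₂ + z_power = 3.539.

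**Check of the method on H1(a).** The bracket is (1 + 4 × .819)/5 + 10.54 × .032 = .855 + .337 = 1.192. That leaves 225/1.192 ≈ 189 effective participants per arm. At a control proportion of 65%, alpha .05 and power .80, the detectable difference is 13.0 points, odds ratio 1.91. Both equal the article's figures.

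**The stated Aim 2 figure.** With no clinic term:
- ICC .003: 3.539 × √(.00889 × .2024) = .150
- ICC .542: 3.539 × √(.00889 × .6336) = .266

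The stated .10 to .13 is not reproduced. If all 450 × 5 = 2,250 observations were independent, d would be 3.539 × √(4/2250) = .149 (.139 one-sided), so .13 is out of reach at any non-negative ICC. Reading 450 as the number per arm gives .106 to .188, which does not match either.

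**H2(d) over a range of assumed ICCs.**

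| Person-level ICC | d, no clinic term | d, clinic ICC .032 |
|---|---|---|
| .542 (top of stated range) | .266 | .329 |
| .61 | .277 | .338 |
| .76 | .300 | .357 |
| .91 | .321 | .375 |

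The clinic ICC of .032 is the article's value for viral suppression, so its use for cognition is also an assumption.

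**Like for like.** Moving the person-level ICC from .542 to .61–.91 raises d by 4% to 21% without a clinic term (.277/.266 and .321/.266), and by 3% to 14% with it (.338/.329 and .375/.329). At d = .13 and no clinic term, power is about 17% at an ICC of .542 and about 10% at .91, against the 80% stated.

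**The case against.** The strongest reply is that borrowing ICCs from related measures is ordinary practice for a new instrument, so the fault is only a missing label. Borrowing is indeed acceptable. But the sentence covers H2(d) and gives its ICCs a source that holds no cognitive data, so the label is needed. The section on developmental trajectories says mediator data will exist at 10 time points, which might suggest earlier cognitive data, but the two explicit statements that cognition is new to Round 2 govern.

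A reader might go further and infer that the Table 2 reliabilities put cognition's ICC above .542. The article does not support that. Internal consistency says nothing about correlation between yearly scores, and short-interval retest reliability is at best a rough ceiling on it. The same table gives "0.77 0.69 0.91" for the family support scales, while ICCs for change mechanisms in the original study are put at no more than .542. If reliability equalled the ICC, those two facts would clash. If part of the .003 to .542 range is clinic-level, test reliability has no bearing on that part. The person-level ICC of .819 for viral suppression shows that high values occur in this cohort, but for a different outcome.

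It is also fair to object that the contrast between .28–.38 and .10–.13 comes mostly from a different defect. That stands.

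**Conclusion.** The power stated for H2(d) rests on an ICC that cannot have come from the named source. It should be presented as an assumption. A value above .542 is plausible but not established.

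Under the assumptions listed, the detectable d for cognition is about .27 (ICC .542) or .28 to .32 (ICC .61 to .91) without clinic clustering, and about .33 or .34 to .38 with a clinic ICC of .032. A reader might attribute the whole gap from .10–.13 to cognition's ICC, or conclude that H2(d) is clearly the weakest-powered Aim 2 hypothesis. Neither is supported: the ICC accounts for at most .055 in d (.321 − .266), and the rest arises because .10 to .13 does not follow from the article's inputs for any Aim 2 outcome.

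The point still survives correction of that error, because a corrected range of .150 to .266 would have no more basis for cognition than the present one. It is worth fixing, though it does not threaten the design.

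**What to change.** Remove H2(d) from the joint power sentence and give it its own: no ICC for cognition is available from the original study; the person-level ICC is assumed over a stated range such as .542 to .91; the corresponding d is .27 to .32 without clinic clustering and .33 to .38 with an assumed clinic ICC of .032. State whether the .003 to .542 range is clinic- or person-level. Make the change together with the correction of .10 to .13 for the other Aim 2 hypotheses, since correcting cognition alone would leave the statement wrong. The cost is one restated sentence.

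Optionally, add age at enrolment, sex and caregiver education, all listed in Table 2 or known from enrolment, as fixed effects in the H2(d) model. If they explained 10% to 20% of the variance of the time-averaged score, d would fall by 5% to 11% (1 − √.9 and 1 − √.8). That share is an assumption, and the model would then differ from the common Aim 2 specification, so the correction does not depend on it.

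### The Aim 2 minimum detectable effects (d = .10 to .13) cannot follow from the stated inputs: even fully independent observations give about .15

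*Protocol article*

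**What the plan says.** The section Statistical Power Analysis for Aims 1 and 2 sets common inputs for every power calculation: "power=.80 and 5 repeated assessments from N=450 participants conservatively assuming 20% attrition". For H2(a) to H2(g) it keeps those inputs and adds "α=.007, and a range of ICCs from .003 to .542 for change mechanisms". It then reports that d "ranged from .10 to .13, which are small standardized effect sizes", and closes by claiming enough power for small to small-to-medium effects in many settings.

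The section Primary Analyses for Aim 2 confirms the alpha, which "will be set at .05/7=.007 for each planned time-averaged comparison". The test is therefore a time-averaged difference between arms. The model's listed fixed effects are study arm, time and their interaction, with no covariates.

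**The concern.** The number of observations sets a limit on what the study can detect, whatever the ICCs are. With 450 people seen 5 times there are at most 2,250 observations, about 1,125 per arm. A threshold of .007 is demanding, and a detectable d of .10 looks too small for that amount of information even before any allowance for correlation within persons or clinics.

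The Aim 2 hypotheses are labelled primary for that aim and cover sexual risk, adherence self-efficacy, economic stability, cognition, mental health, social support and prosocial transitions. If the published sensitivity is too optimistic, a reader of a null Aim 2 result could take effects of .10 to .13 to have been tested with 80% power when the actual power was well below that.

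**Working it through.** **Inputs.** From the power section: power .80, N = 450 (562 × 0.8 = 449.6), m = 5 assessments, alpha .007, ICCs .003 to .542. From the Methods overview of the original study: 39 clinics, 344 control and 358 intervention participants, so close to 1:1. Assumptions: equal arms of 225 and, unless noted, a two-sided test.

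**Formula.** For a time-averaged difference,

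d = (z for alpha + z for power) × sqrt(2 × DE / (225 × 5)),

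DE = 1 + (m − 1) × person ICC + m × (k − 1) × clinic ICC, with k = 450/39 = 11.54 persons per clinic.

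**Check on the article's own H1(a) figure.** With 65% control suppression, alpha .05, person ICC .819 and clinic ICC .032:

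- DE = 1 + 4 × .819 + 5 × 10.54 × .032 = 5.96, so the effective size is 1,125/5.96 = 188.7 per arm.
- Power for 65% against 78% is .801. The odds ratio is (.78/.22)/(.65/.35) = 1.91 and h = .29.

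These match the stated 13 points, 1.91 and .29, so the method agrees with the article for H1(a).

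**Floor for Aim 2 (both ICCs zero, DE = 1).**

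- Two-sided: (2.697 + 0.842) × sqrt(2/1125) = .149.
- One-sided: (2.457 + 0.842) × sqrt(2/1125) = .139.

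Both exceed .13. Solving for sample size, d = .10 needs about 2,504 independent observations per arm and d = .13 about 1,482, against 1,125 available.

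**Across the stated ICC range, read as person-level (two-sided alpha .007).**

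| Clinic ICC | d at person ICC .003 | d at person ICC .542 |
|---|---|---|
| 0 | .150 (DE 1.012) | .266 (DE 3.168) |
| .003 (illustrative) | .161 | .272 |
| .032 (H1(a) value, assumed to apply) | .245 | .329 |

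One-sided with no clinic ICC, the range is .140 to .248. The actual slight imbalance between arms does not change the two-sided figures to three decimals.

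**Width of the range.** With no clinic ICC, moving the person ICC from .003 to .542 should widen d by sqrt(3.168/1.012) = 1.77. The stated range widens by .13/.10 = 1.3.

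**Power at given effects (two-sided alpha .007).**

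| d | ICC 0 (ceiling) | Person .003, no clinic ICC | Person .542, no clinic ICC |
|---|---|---|---|
| .10 | 37% | 37% | 9% |
| .13 | 65% | 64% | 17% |
| .20 | 98% | 98% | 49% |

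With a clinic ICC of .032, power for d = .20 is 58% at person ICC .003 and 29% at .542.

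**Where 80% power for d = .20 ends.** DE may be at most (.20/.1492)² = 1.80. With no clinic ICC, that allows a person ICC up to .80/4 = about .20. With a clinic ICC of .032, the clinic term alone adds 5 × 10.54 × .032 = 1.69, so no person ICC is low enough.

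**Other readings tried.** Alpha .01 and .05, one-sided tests, N of 562, 702 and 900, 10 time points, a slope contrast and Cohen's f were tried. None returns both ends of the stated range.

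**The case against.** The floor itself stands: neither a one-sided test nor the arm imbalance brings d down to .13. Four objections limit what can be built on it.

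- **Small effects are not out of reach.** A reader might infer that the study cannot detect small effects at all. The article does not support that. It labels h = .20 as small, and power for d = .20 is about 98% when the person ICC is .003 and there is no clinic clustering. It falls to 49% at .542, so the answer depends on the outcome. The closing sentence already speaks of small to small-to-medium effects, and it needs a qualification rather than removal.
- **No single replacement range follows.** The article says only "a range of ICCs from .003 to .542 for change mechanisms" and does not give the level. It is also unclear whether the H1(a) clinic ICC is among the inputs carried over. The article supports a value of at least about .15. The .15 to .27 range is conditional on a person-level reading and no clinic clustering.
- **The cause is unknown.** It is tempting to suggest that the repeated measures were treated as independent, but that reading gives .149 itself. An N of 562 with full independence gives .1335, which rounds to .13, but that is not the stated N and does not produce the .10.
- **The consequences are limited.** The cohort already exists, N was not derived from this figure, and H1(a) is unaffected. Nothing in the article says that null results will be interpreted from the planned detectable d.

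All four stand. They narrow the point without rescuing the stated figure.

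**Conclusion.** Wrong as written. A detectable d of .10 to .13 cannot be obtained from "5 repeated assessments from N=450 participants" at alpha .007 and power .80. The bound of .149 two-sided (.139 one-sided) assumes only roughly equal arms, a normal approximation and no negative correlation. It does not depend on which level the ICCs describe.

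On the person-level reading, the detectable effect is .15 to .27 with no clinic clustering, against the stated .10 to .13. That is about 1.5 times the stated value at the lower end (.150/.10) and 2.0 times at the upper end (.266/.13). It is larger still if clinic clustering of the H1(a) size applies, which is an assumption. This is a reporting error in the sensitivity claimed for Aim 2. The design, the alpha allocation, the model and the Aim 1 calculation are untouched.

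**What to change.** Rerun the Aim 2 calculation with N = 450, 5 assessments and alpha .007. State whether the test is one- or two-sided, and give the person-level and clinic-level ICC for each outcome or the range at each level. Replace .10 to .13 with the result, which will be at least about .15 for a two-sided test.

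Qualify the closing sentence so that 80% power for a small effect (about d = .20) is claimed only for outcomes with low ICCs at both levels. For high-ICC outcomes, claim only small-to-medium effects.

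The cost is a rerun and two revised sentences, with a less favourable figure. Sample size, hypotheses and analysis model stay as they are.
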